***Regression diagnostics***

Diagnostic checks to assess the appropriateness of the regression models fitted will be through the use of residual plots. We will plot:

- Histograms and probability plots of the residuals to assess normality
- Scatter plots of residuals against fitted values to assess constant variance and linearity, and to identify potential outliers.

Should the normality assumption be untenable for the continuous outcomes, bootstrap methods will be applied to estimate the confidence intervals of the treatment effects.

**Objective 6.** What is the estimated sample size for a fully powered trial to evaluate the effectiveness of iMAPS-2 (relative to usual care)?

**Outcomes**

Positive and Negative Syndrome Scale (PANSS), Psychotic Symptom Rating Scales (PSYRATS), Questionnaire about the Process of Recovery (QPR) and Brief Core Schema Scale (BCSS)

**Analysis**

The analyses described for Objective 4, together with the findings of the qualitative analysis that will consider the views of the participants on the candidate primary outcome measures, will be used to ‘shortlist’ a potential primary outcome measure(s). We will also consider the feasibility of running a full effectiveness trial with each of those candidate outcomes remaining after this process, by considering the respective sample sizes required to detect a specified MID to assist with our decision-making. We will discuss our findings and proposals with the Trial Steering Committee to help inform our recommendations for a full effectiveness or evaluation trial.

### Sensitivity analyses

Follow-up outcome assessments are performed at 16 weeks (end-of-therapy assessment) and 28 weeks (follow-up assessment), although there is no formal time window to maximise completion of outcome data as stated in section 4.8. From a feasibility perspective to report the frequency (%) of participants completing the assessments within a reasonable timeframe (i.e., within 4 weeks of the scheduled time-points).

If the proportion of scheduled assessments completed more than 4 weeks after the scheduled date for any time-point is ≥10%, we will repeat the efficacy analyses for objective 4 excluding the ‘out of window’ assessments. This will help to explore the consideration of data collection and practicalities around introducing a ‘completion window’ for a full trial.

## Subgroup analyses

N/A

## Missing data

As this is a feasibility study we will focus on reporting the amount of missing data (see sections 6.4). We will report the number (%) of participants withdrawing fully from the trial and lost to follow-up by treatment arm. Reasons for missingness may be important and these will be tabulated by treatment arm and documented as far as possible.

We will also tabulate the number of missing items within questionnaires (see Objective 3, section 7.2).

Efficacy analyses of clinical outcomes are adjusted for baseline values. If there are any missing baseline values of the corresponding outcome data, we will use simple mean imputation (across the groups) to avoid exclusion of such participants in the proposed complete-case analysis [21].

## Additional analyses

There are 3 additional analyses planned:

1. We will tabulate the PANSS response rates:

- Deterioration or no change (Negative or 0% reduction from baseline)
- >0% but <25% reduction from baseline
- 25% to <50% reduction from baseline
- 50% to <75% reduction from baseline
- 75% to <100% reduction from baseline
- 100% reduction from baseline

at 16 and 28 weeks by treatment arm to show how many participants are still symptomatic at the end of treatment and follow up, and how many have responded and to show the overall amount of change.

1. To assess the extent of unblinding, we will report the frequency (%) of recorded instances where outcomes assessors reported to be unblinded, overall and by randomised group.
2. We will summarise the individual items of the brief imagery interview (shortened version of Schulze et al. , 2013) where participants describe the images (from 1 image to 3 images) they experienced in relation to your psychosis:
3. Image frequency in past week (0 = images have not occurred 1 = images occur once a week; 2 = images occur a few times a week; 3 = images occur once a day; 4 = images occur multiple times a day)
4. Image frequency in past month 0 = images have not occurred 1 = images occur once a week; 2 = images occur a few times a week; 3 = images occur once a day; 4 = images occur multiple times a day
5. Image Distress (0-100) where 0 is not distressing at all and 100 is the most distressing it could be.

We will tabulate items 1 and 2 and present frequencies (%) of the endorsed individual items. Images reported and Image distress will be summarised by mean (SD) or median (IQR) as appropriate.

Results will be presented by allocated treatment and time point (i.e., Baseline, 16 weeks and 28 weeks).

1. The reporting of harms, as described in the next section.

## Harms

The number of safety events (e.g., AEs and SAEs) and number (and proportion) of participants reporting at least one safety event will be summarised by treatment arm. Summary measures will be number (%).

Safety events will also be tabulated by:

- Death by suicide
- Suicide attempt
- Suicidal crisis without attempt (rating 2 on item 8 of Calgary Depression Rating Scale for Schizophrenia CDSS)
- Severe symptoms increase (rating of > 6 on the patient or researcher rated CGI and CGI-I)

They will be reported by both overall and by treatment arm.

Treatment effects will be estimated by the difference in event rates and 95% CI for the differences.

In addition, we will tabulate and present frequencies of the endorsed individual items in the Adverse Effects in Psychotherapy (AEP) scale (29) for those participants allocated to the intervention arm. This is a self-report measure of potential adverse effects completed by the participants at the end of therapy assessment measuring 7 broad categories: worsening difficulties, poor engagement (including low motivation), situational change, no benefit from therapy, stigma, conflict with others (family, care team) and feeling better.

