**Exclusion Criteria**

1. primary diagnosis of alcohol, substance misuse disorder, or bipolar disorder (affective psychosis)
2. Secondary presenting difficulties such as severe addiction, acute suicidal risk, dementia, neurological disorder.
3. developmental disability (moderate to severe learning difficulty)
4. acquired brain injury/organic syndrome
5. currently participating in physical or mental health treatment studies or receiving psychological therapy
6. unable to complete the measures in written English (due to assessment battery psychometric validation in English)
7. in forensic settings
8. unmanageable level of risk of violence to researchers or clinicians (harassment behaviour – stalking).

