## Blinding

To reduce detection bias, researchers undertaking assessments will be blind to the allocation. The success or otherwise of our attempts at blinding will be recorded. Where a research assistant is unblinded, another research assistant will make an appointment to undertake the assessment.

*Allocation concealment (from both recruiting staff member and [potential] participant) will be ensured, as the system will not release the randomisation code until the participant has been randomised which takes place after all baseline measurements have been completed*.

.

It is not anticipated that un-blinding of the research assistants will occur in the trial and it is not expected that there would be any reason for emergency un-blinding of the researchers. Any instances of unintentional un-blinding will be recorded.

The Trial Statistician will remain blinded to treatment allocation until after the Statistical Analysis Plan (SAP) have been sign off and the analysis of unblinded data commences.

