| **Serious Adverse Event (SAE)** | A serious adverse event is any untoward medical occurrence that:   - results in death - is life-threatening - requires inpatient hospitalisation or prolongation of existing hospitalisation - results in persistent or significant disability/incapacity - consists of a congenital anomaly or birth defect   Other ‘important medical events’ may also be considered serious if they jeopardise the participant or require an intervention to prevent one of the above consequences.  NOTE: The term "life-threatening" in the definition of "serious" refers to an event in which the participant was at risk of death at the time of the event; it does not refer to an event which hypothetically might have caused death if it were more severe.  In line with an approach previously used (Pyle et al 2016) which was adapted from Klingberg et al 2012), in addition we will define serious adverse events as:   1. death by suicide 2. suicide attempt 3. suicidal crisis without attempt (rating 2 on item 8 of Calgary Depression Rating Scale for Schizophrenia CDSS) 4. severe symptoms increase (rating of > 6 on the patient or researcher rated CGI and CGI-I). |
| **Serious Adverse Reaction (SAR)** | An adverse event that is both serious and, in the opinion of the reporting Investigator, believed with reasonable probability to be due to the psychological therapy/assessment or qualitative interview, based on the information provided. |
| **Related and Unexpected Serious Adverse Reaction** | A serious adverse reaction, the nature or severity of which is not consistent with the effects or consequences of a psychological intervention. |

NB: to avoid confusion or misunderstanding of the difference between the terms “serious” and “severe”, the following note of clarification is provided: “Severe” is often used to describe intensity of a specific event, which may be of relatively minor clinical significance. “Seriousness” is the regulatory definition supplied above.

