Our iMAgery focused therapy for Psychosis approach has previously been tested in a case series and no severe adverse events were reported. Building on work by others in psychological treatments for psychosis, we wish to carefully record and report adverse events of psychological interventions and wish to implement a protocol developed assessing and managing any such risk, which will be completed at end of treatment and at follow up by research assistants who are blind to the allocated group. We are adding the use of the CGI and additional criteria below.

This protocol will also be completed by clinicians during the intervention, that is each session, to complete an assessment of severe adverse events, for clinical purposes.

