## Analysis populations

Feasibility analyses will include all the consented participants to estimate the proportion of eligible consented participants and eligible participants randomised. To summarise the number of iMAPS-2 therapy sessions attended, we shall include all the participants allocated to the intervention group. The proportion of adherent participants (attending at least 3 sessions of the iMAPS-2 therapy) will include all the participants allocated to the intervention group.

Analyses of efficacy will be by intention-to-treat (ITT), where all randomised participants for whom outcomes are available will be analysed in their allocated group regardless of their adherence to therapy.

The safety population will also follow the ITT principle and it will comprise all randomised participants.

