## Baseline patient characteristics

We will summarise the following demographic characteristics both overall and by randomised group:

- Gender (Male/Female/Non-binary/Other)
- Age (years)
- Chart Diagnosis (ICD-11) Schizophrenia, Schizoaffective disorder, delusional disorder, Schizophreniform disorder, Unspecified (non-affective) psychosis – FEP, other.
- ICD-11 Code
- Illness severity as measured by the positive and negative syndrome scale (PANSS), (Mildly ill/Moderately ill/ Markedly ill/ Severely ill)
- Highest education level (Primary school/secondary school/Further education (e.g. College)/Higher education (e.g. University)
- Employment status (Full Time/Part Time/Retired/Voluntary/Student/ Home duties/ Unemployed)
- Marital status (Single/Married/Living with partner/Civil Partnership/Separated/ Divorced/Widowed)
- Living arrangements. Who does the person live with? (Spouse/Partner only, Spouse/Partner plus children, Spouse/Partner plus other/s (not children), Alone, Children only, Parent/s only, Friend/s only, Supported accommodation/hostel, Other)
- Index of Multiple Deprivation (IMD) Decile (derived from Postcode) (adjacent categories will be merged to form three broader categories: 1-3; 4-7; 8-10)
- Ethnicity (Bangladeshi/Indian/Pakistani/Any other Asian background/African/Caribbean/ Any other Black background/ White & Asian/White & Black African/ White & Black Caribbean/ Any other mixed background/ British/ Irish/Any other White background/ Chinese/Any other ethnic group/ Prefer not to answer)
- Treatments received (i.e. past therapy) and current treatment.
- Service type (Early Intervention Psychosis Team, CMHT, Inpatient)
- Inpatient/Outpatient status and legal status will also be reported
- BAI-rated Anxiety (minimal anxiety (0-7), mild anxiety (8-15), moderate anxiety (16-25), severe anxiety (26-63),).
- CDSS rated depression (minimal or absent (0-6), possible major depressive episode(7-27))

Summary measures for the baseline characteristics of each group and overall will be presented as mean and standard deviation, and median and interquartile range (IQR) for continuous variables, and frequency and percentage for categorical variables.

The categories for some of the variables such as ‘Living arrangements’ or ‘ethnicity’ might need to be merged at the time of analysis given the large number of categories and relatively small sample size.

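### SHEAP 7.6 counts a CDSS item 8 rating of 2 as a suicidal crisis without asking whether it is new, so the arm difference mixes new crises with unresolved baseline ones

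*Combined protocol and SAP*

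**What the plan says.** SHEAP 7.6 (Harms) tabulates safety events in four categories. The third is "Suicidal crisis without attempt (rating 2 on item 8 of Calgary Depression Rating Scale for Schizophrenia CDSS". Protocol 3.17 lists the same criterion among serious adverse events: "suicidal crisis without attempt (rating 2 on item 8 of Calgary Depression Rating Scale for Schizophrenia CDSS". Neither text compares the rating with an earlier one. SHEAP 7.6 then says: "Treatment effects will be estimated by the difference in event rates and 95% CI for the differences".

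Other provisions that bear on the point:

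- SHEAP 5.3: "The safety population will also follow the ITT principle and it will comprise all randomised participants".
- The assessment table in protocol 3.11 schedules the Calgary scale at baseline, 16 weeks and 28 weeks.
- Protocol 3.10 says of randomisation: "which takes place after all baseline measurements have been completed". Every participant is therefore due a pre-randomisation item 8 rating.
- Protocol 3.17 says of the adverse-event assessment: "which will be completed at end of treatment and at follow up by research assistants who are blind to the allocated group".
- The exclusion criteria include "Secondary presenting difficulties such as severe addiction, acute suicidal risk, dementia, neurological disorder", with no item 8 threshold.
- Protocol 3.18 confines recording to events related to the therapy, assessment or interview that arise from baseline to the end of the study.

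**The concern.** A between-arm difference labelled a treatment effect is naturally read as events that arose after allocation. Under the rule as written, a crisis present before randomisation and not resolved by 16 or 28 weeks counts in the same way as a new one, and no row separates the two. The efficacy analyses, including that of the total of this same scale, adjust for baseline (SHEAP 7.2 and 7.4); this category makes no use of it.

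Baseline item 8 ratings of 2 are plausible in this population. SHEAP 6.5 uses the bands "CDSS rated depression (minimal or absent (0-6), possible major depressive episode(7-27", and Supplementary Table 3 gives an overall baseline lower quartile of 7, so about three quarters of participants were in the upper band. That says nothing directly about item 8.

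At stake is how readable the comparative suicidality evidence handed to the definitive trial will be. For a therapy that works with upsetting memories, new suicidal crises are a separate safety question from crises that fail to resolve.

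**Working it through.** **The plan's own figure.** The SHEAP states no precision target for harms. Its only one is for retention (protocol 3.21, SHEAP 4.4): an exact 95% interval no wider than 25% if at least 80% of 45 are retained. At 36/45 the Clopper-Pearson interval is 65.4% to 90.4%, width 25.0 points, so the figure reproduces to rounding. It also supplies the 36 used below.

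**Inputs.**
- From the documents: 30 v 15 planned; at least 36 with outcome data, taken as 24 v 12 at the same 2:1 ratio.
- Assumed, because no item 8 data are given: baseline prevalence of a rating of 2, p = 2% to 20%; persistence to follow-up, q = 50% or 100%; new-event rate among those not rated 2 at baseline, e = 15% for iMAPS and 5% for TAU.
- Relapses (2, then lower, then 2 again) are ignored.

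**Weight of one case.** At 30 v 15, one persistent baseline case moves the difference by 1/30 = 3.3 points if in iMAPS, or 1/15 = 6.7 points if in TAU.

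**Expected persistent cases,** N × p × q:
- 45 assessed: 45 × 0.20 × 1 = 9.0 at most; 45 × 0.02 × 0.5 = 0.45 to 45 × 0.02 × 1 = 0.90 at 2% prevalence.
- 36 assessed: 36 × 0.20 × 1 = 7.2 at most; 0.36 to 0.72 at 2% prevalence.

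**Chance imbalance from persistent cases alone.** With r = pq, SD = √[r(1−r)(1/30 + 1/15)]. At p = 0.05, q = 0.5 this is 0.049. At p = 0.20, q = 1 it is √[0.20 × 0.80 × 0.10] = 0.126. At p = 0.02 it is 0.031 to 0.044. The mean is zero when persistence is equal in the arms.

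**Interval width.** The emergent rate is (1−p)e and the all-ratings rate is pq + (1−p)e. The table gives the expected Newcombe 95% half-width as a proportion, summed exactly over both binomial distributions.

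| p | q | 30 v 15: emergent | all | ratio | 24 v 12: emergent | all | ratio |
|---|---|---|---|---|---|---|---|
| 0.02 | 0.5 | 0.2043 | 0.2081 | 1.02 | 0.2332 | 0.2367 | 1.02 |
| 0.02 | 1 | 0.2043 | 0.2117 | 1.04 | 0.2332 | 0.2402 | 1.03 |
| 0.05 | 0.5 | 0.2032 | 0.2126 | 1.05 | 0.2322 | 0.2409 | 1.04 |
| 0.10 | 1 | 0.2014 | 0.2346 | 1.16 | 0.2305 | 0.2617 | 1.14 |
| 0.20 | 1 | 0.1978 | 0.2551 | 1.29 | 0.2270 | 0.2812 | 1.24 |

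The expected difference is the same under both counts within each row. At p = 0.10 it is 0.135 − 0.045 = 0.090.

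**Unequal persistence,** p = 0.10, emergent difference 9 points throughout:
- Half persist in iMAPS, all in TAU: (0.05 + 0.135) − (0.10 + 0.045) = 0.185 − 0.145 = 4 points.
- The reverse: (0.10 + 0.135) − (0.05 + 0.045) = 0.235 − 0.095 = 14 points.

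Both all-ratings figures are correct for what they measure. The reader simply cannot see which component produced them.

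**The case against.** The best defence is that the all-ratings count is a sound intention-to-treat contrast. The share of each randomised arm found in suicidal crisis after randomisation covers both new crises and failure to resolve. Both matter, and counting both is cautious for safety. This stands, and it is why the count should be kept.

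Second, two provisions limit carry-over. Protocol 3.18 looks to related events arising after baseline, and an unchanged state is arguably not such an event. Acute suicidal risk is an exclusion. Both may lower the number of persistent cases, but neither removes them under SHEAP 7.6 as written: that section carries over no onset or relatedness condition, Supplementary Table 6 reports unrelated suicidality events by arm, and the exclusion is not tied to item 8.

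Third, the magnitudes rest on unsourced prevalence, persistence and event rates, and assessing all 45 is optimistic. This is fair. It is the reason for showing the 2% case and the 36-assessed case.

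Fourth, SHEAP 7.6 does not say whether the difference is taken for each category or for all events together. If only for all events, item 8 is one component of a composite and the half-widths above do not apply to the reported contrast.

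A reader might also take the 8 v 3 events of suicidal ideation with a plan in Supplementary Table 6 as the item 8 count and re-analyse them. The documents do not support that: the table lists them as adverse events, whereas protocol 3.17 makes an item 8 rating of 2 a serious one, and no text links the two.

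**Conclusion.** The point holds as one of interpretation and precision. A persisting pre-randomisation rating of 2 meets the written rule and enters the tabulated count, and also the difference if that is taken by category.

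Under the stated assumptions the expected half-width is about 2-29% wider than for emergent events with all 45 assessed, and about 2-24% wider with 36. At most 9.0 or 7.2 persistent cases are expected, and fewer than one at 2% prevalence. The true number is unknown.

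Three stronger readings are not supported:
- **Bias.** Carry-over does not bias the comparison. Under randomisation with equal persistence the expected difference is unchanged, and unequal persistence would itself be an effect of treatment.
- **Baseline ratings scored as events.** The adverse-event assessment is completed at end of treatment and follow-up, so the baseline rating itself is not counted.
- **A decision at risk.** The progression criteria concern recruitment, retention and adherence, and SHEAP 4.6 sets no statistical stopping rule. Nor is power the argument, since the trial is not powered for between-group differences.

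This is a cheap improvement to the safety table, not the repair of an invalid analysis.

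**What to change.** In SHEAP 7.6 keep the all-ratings count and its difference. For this category add:

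- the number of participants by arm, and the risk difference with 95% CI, for emergent events: an observed post-randomisation item 8 rating of 2 that is higher than the participant's baseline rating or than an earlier post-randomisation rating, so that a relapse after improvement counts;
- baseline item 8 ratings by arm;
- persistent baseline cases by arm in their own row, so that any effect of therapy on resolution stays visible;
- missing item 8 ratings by arm.

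Use observed item 8 ratings only. SHEAP 7.1 lets a Calgary total stand with up to three items filled by the mean of the others, and such a value should not create or remove an event. For the same reason, the 45 baseline totals in Supplementary Table 3 do not guarantee 45 baseline item 8 ratings, so availability needs checking.

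The cost is some SHEAP wording, a few extra table rows and a second contrast to interpret. No new data are collected, and event recording, sponsor reporting and steering committee review stay as they are.

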**Full Trial Progression Criteria:**

We will progress to a full trial if we all our criteria below are classed as GREEN; if one or more is AMBER, we will investigate whether it is possible to make adjustments to the trial design to overcome any problems and, if that appears possible, progress to a full trial (including an assessment of the success of our adjustments in its internal pilot, where appropriate); if one or more is RED, we will not progress unless we can make the substantial amendments which would be necessary to make a full trial feasible.

1. Recruitment: GREEN: >=80% (n>=36) of target recruited; AMBER >=40 % (n=18-35)-< 80% of target recruited; RED <40% (n<18) of target recruited.
2. Retention: GREEN: >=80% of participants providing 16-week outcome data ; AMBER: >60%- <80% of

participants providing 16-week outcome data; RED: <60% of participants providing 16-week outcome data.

- 1. Adherence: GREEN>=75% adherence of participants attend at least 5 sessions of therapy, AMBER>=40% participants

attend at least 5 sessions of therapy; RED: <40% of participants attend at least 5 sessions of therapy (based on Jolley et al. 2015).

Assessment Measures

|  | **Procedures and Questionnaires** | **Mins** | **Baseline** | **16 Weeks Follow Up** | **28 Weeks Follow Up** |
| --- | --- | --- | --- | --- | --- |
|  | Demographics | 5 | X | As needed | As needed |
| **Psychosis Measures** | PANSS | 60 | X | X | X |
|  | PSYRATS | 15 | X | X | X |
|  | QPR | 5 | X | X | X |
| **Imagery** | Brief Imagery Interview  Visual Analogue Scales/MIPQ  Psychosis Imagery Questionnaire (PIQ) | 10  5 | X  X | X | X |
| **Schemas** | BCSS | 2 | X | X | X |
| **Trauma** | TALE | 5 | X |  |  |
|  | ITQ | 5 | X | X | X |
|  | BES | 5 | X | X | X |
| **Mental Health and Functioning** | BAI | 5 | X | X | X |
|  | CDS | 9 | X | X | X |
|  | WEMWBS | 5 | X | X | X |
|  | PSP | 10 | X | X | X |
| **Health Economics** | EQ-5D-5L | 2 | X | X | X |
|  | ReQoL-10 | 2 | X | X | X |
|  | Economic Patient Questionnaire | 10 | X | X | X |
|  |  |  |  |  |  |
| **Working Alliance** | WAI-client | 5 | 3^rd^ Session | 6^th^ | 9^th^ |
|  |  | 5 |  |  |  |
| **THERAPIST ONLY** | WAI-therapist | 5 | 3^rd^ Session | 6^th^ | 9^th^ |
|  | iMAPS therapy fidelity Checklist  CTS-R or CTS-Psy |  | A selection of therapy sessions will rated in supervision and by an independent external therapist |  |  |
| **Adverse Effects** | CGI-IP | 1 | Each Session |  |  |
|  | CGI-SP | 1 | Each Session |  |  |

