# Trial Methods

## Trial design

This is a feasibility assessor-blind RCT comparing treatment as usual (TAU) plus iMAPS-2 therapy, versus TAU, in a 2:1 allocation ratio.

Participants allocated to the intervention arm received 12 sessions of individualised iMAPS-2 psychological therapy.

iMAPS-2 will also look at the feasibility of establishing the optimum way of evaluating cost-effectiveness.

In addition, iMAPS-2 has a nested qualitative study design of participants’ experiences of iMAPS-2 intervention and trial participation, to identify themes relating to the acceptability of this therapy and inform parameters of the definitive trial including therapy protocol, outcome measures, recruitment and retention. However, the qualitative analysis will not be performed by the Trial Statistician or Health Economist and therefore is not described in this document.

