***Adverse Effects***

### Clinical Global Impression- Improvement (CGI-I)

The CGI I is a stand-alone measure rating the change from baseline to treatment. The CGI I is rated on a 7-point scale: 1=very much improved since the initiation of treatment; 2=much improved; 3=minimally improved; 4=no change from baseline (the initiation of treatment); 5=minimally worse; 6= much worse; 7=very much worse since the initiation of treatment [20].

Participant and therapist versions will be reported separately.

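### SHEAP 7.6 compares harm rates between arms without fixing the source of events, although only the iMAPS arm has a harms check and CGI at every therapy session

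*Combined protocol and SAP*

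**What the plan says.** **The comparison.** SHEAP 7.6 (Harms) counts adverse and serious adverse events, and participants with at least one, by arm. It also tabulates four specific categories, one of them "Severe symptoms increase (rating of > 6 on the patient or researcher rated CGI and CGI-I" scales. Treatment effects are then estimated as differences in event rates with 95% CIs. No source of events is specified or excluded. Protocol 3.17 makes the same CGI criterion, "severe symptoms increase (rating of > 6 on the patient or researcher rated CGI and CGI-I" scales, part of its definition of a serious adverse event.

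**The schedule.** The Assessment Measures table in Protocol 3.11 lists "CGI-IP | 1 | Each Session", gives CGI-SP the same timing, and shows no CGI entry for 16 or 28 weeks.

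**The two tiers of checking.** Protocol 3.17 describes a harms protocol, says the CGI is being added, and states that the protocol is one "which will be completed at end of treatment and at follow up by research assistants who are blind to the allocated group". It continues: "This protocol will also be completed by clinicians during the intervention, that is each session, to complete an assessment of severe adverse events", and gives the purpose of that extra check as clinical.

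**The number of sessions.** SHEAP 4.1: "Participants allocated to the intervention arm received 12 sessions of individualised iMAPS-2 psychological therapy".

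**The AEP questionnaire.** Protocol 3.17 defines non-severe adverse events by an AEP item score. The AEP is given on completing therapy, or sent to those who leave it early. SHEAP 7.6 tabulates it for the intervention arm only.

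**The concern.** A difference in event rates measures harm only if both arms have a similar chance of having an event noticed. Here one arm can be checked up to 12 more times than the other, and for some event types usual care may have no route to detection at all. If the extra checks feed the count, the planned difference mixes any effect of therapy with intensity of surveillance, and the 95% CI covers neither the bias nor its size. An excess in iMAPS could be a false signal, or a true one could be dismissed as the product of more looking. Adverse events are a listed outcome (Protocol 3.11), and the trial is meant to inform a definitive one.

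**Working it through.** The plan states no figure for harms, so there is none to reproduce. The check is how large a gap unequal looking would create when true risk is identical.

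**Inputs from the documents**
- Session checks, iMAPS only: up to 12 (SHEAP 4.1), over a twelve-week therapy phase (Protocol 3.16).
- Blinded research checks, both arms: 2, at end of treatment and follow-up (Protocol 3.17), i.e. 16 and 28 weeks.
- Looks: iMAPS 12 + 2 = 14; usual care 2.
- Planned arm sizes: 30 and 15 (Protocol 3.1).

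**Assumption.** Each look has the same, independent chance p of a qualifying finding in either arm. No document gives p, so a range is shown.

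**Formula.** P(at least one recorded event) = 1 − (1 − p)^k, where k is the number of looks.

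| p per look | iMAPS, k = 14 | Usual care, k = 2 | Spurious gap (points) |
|---|---|---|---|
| 0.25% | 3.4% | 0.5% | 2.9 |
| 0.5% | 6.8% | 1.0% | 5.8 |
| 1% | 13.1% | 2.0% | 11.1 |
| 2% | 24.6% | 4.0% | 20.7 |

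At p = 1%, the expected numbers of participants with an event are 30 × 0.1313 = 3.9 and 15 × 0.0199 = 0.3, a ratio of proportions of 6.6.

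**Fewer sessions.** With 5 sessions attended (the adherence threshold), iMAPS has 5 + 2 = 7 looks. At p = 1% this gives 6.8% against 2.0%: a gap of 4.8 points and a ratio of 3.4.

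**CGI taken only at sessions.** If the Protocol 3.11 table is complete, the CGI has 12 looks against 0. At p = 1% this gives 11.4% against 0%, and usual care is zero by construction.

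**Looks that are not independent.** Weekly ratings of one person are correlated. A simulation therefore gave both arms the same episodes, starting at 1% per week over 28 weeks. An episode was detected only if present at a look (weeks 1 to 12 for sessions; weeks 16 and 28 for visits). Onset rate and duration are assumptions.

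| Episode length | iMAPS | Usual care | Gap (points) | Ratio |
|---|---|---|---|---|
| 1 week | 13.0% | 2.0% | 11.0 | 6.6 |
| 4 weeks | 18.2% | 7.7% | 10.5 | 2.4 |
| 8 weeks | 21.3% | 14.8% | 6.5 | 1.4 |

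Longer episodes are more often still present at a research visit, so the ratio falls sharply. The sign does not change in any scenario.

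**With common sources only.** Both arms have k = 2. Under equal risk and equal attendance the expected difference is zero; at p = 1% it is 2.0% against 2.0%.

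**The case against.** **The session check is described as clinical.** On a natural reading of Protocol 3.17, the blinded visits supply the research comparison and the session check is for care. A reader might go further and infer that session events are certainly counted; no passage says so. Equally, none excludes them. Protocol 3.18 sends related adverse events to the CRF from baseline to end of study whatever their source, and requires related serious events to be reported once research staff become aware of them. SHEAP 5.2 describes the therapists as part of the research team. The bias is therefore conditional, and the plan leaves the condition open.

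**Usual care may have a CGI.** SHEAP 7.1 says of the CGI: "Participant and therapist versions will be reported separately". A reader might infer that it exists only where there is a therapist. That does not follow. The same section calls the PANSS therapist-rated, the PSYRATS therapist-administered and the PSP therapist-reported, and all three are scheduled for both arms. The event definition refers to patient or researcher ratings, and Protocol 3.17 may already place a blinded CGI at both visits. This objection stands.

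**Not every event type is exposed alike.** CDSS item 8 is scheduled equally in both arms. Service use, including admissions and A&E, is collected in both. Deaths and suicide attempts can surface through routine care, and both arms receive a wellbeing call 48 hours after each assessment (Protocol 3.6). These points stand. They narrow the problem without removing the extra session looks.

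**Little hangs on the contrast.** SHEAP 5.1 plans no formal tests, progression rests on recruitment, retention and adherence, and SHEAP 4.6 sets no statistical stopping criterion. This also stands and limits the severity.

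**Conclusion.** The point holds in conditional form. SHEAP 7.6 plans a between-arm rate difference with no source restriction, while scheduled harms checking is up to 14 looks in iMAPS and at most 2 in usual care. If session-detected events enter, the contrast is biased towards excess harm in iMAPS. The bias is strongest for CGI-defined severe symptom increase and for AEP-defined adverse events, which usual care cannot generate by that route. It is weaker for death, suicide attempt, admission and CDSS item 8.

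Only the direction is firm. The gap of roughly 3 to 21 points rests on assumed per-look chances of 0.25% to 2% and on independent looks. A qualifying rating must be 7 on a 7-point scale, and the earlier case series reported no severe adverse events, so the lower end may be nearer.

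A reader might take Supplementary Table 6 as proof, since it shows 10 events among 31 iMAPS participants and 3 among 14 in usual care. It does not show this: the counts are small, no source of detection is given, and there is no CGI row. It neither confirms nor refutes the bias.

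This should be fixed as a cheap improvement. It does not undermine the trial's feasibility conclusions.

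**What to change.** 1. In SHEAP 7.6, base the between-arm difference and its 95% CI only on sources common to both arms: the blinded 16- and 28-week assessments, and the same clinical-record or service-use check applied in each arm.
2. List session-detected and AEP-defined events separately for iMAPS, with no between-arm contrast.
3. Reconcile the Protocol 3.11 table with Protocol 3.17 on whether the CGI is taken at the research visits. If it was not, report CGI-defined events for iMAPS only and give no between-arm difference for them.

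**Cost.** The first two changes are analysis and reporting wording, and need each event record to show how the event was found. The appended results show that data have been collected, so scheduling a CGI at both visits for everyone would be a data-collection change for the definitive trial and not something SHEAP wording can supply. The downside is that events seen only in sessions leave the contrast, but they remain listed, so no safety information is lost.
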